During the treatment period, patients will visit the hospital for follow-up at weeks 0, 12 (± 5 days), and 24 (± 5 days). The follow-up will include medication dispensing and management, urine or blood pregnancy test (for females only), physical examinations, vital signs, weight, waist circumference, 12-lead ECG, blood routine test, urine routine test, blood biochemistry, adverse events, HbA1c, fasting blood glucose, fasting insulin + C-peptide, postprandial 2h blood glucose, postprandial 2h insulin + C-peptide levels, and recording of concomitant medications (antidiabetic and other drugs). At weeks 12 (± 5 days) and 24 (± 5 days), fasting fingertip blood glucose and postprandial 2h fingertip blood glucose levels were measured. At week 12 (± 5 days), CGM was performed for approximately five days. One week (± 3 days) after the end of treatment, a telephonic follow-up will be conducted to record adverse events and concomitant medications (antidiabetic and other drugs).

Patient satisfaction, quality of life, and adherence were evaluated using DTSQ, DQOL questionnaire, and ARMS-D. The patients completed the DQOL questionnaire at week 0 and the DTSQ, DQOL questionnaire, and ARMS-D at weeks 12 and 24.

All patient data related to the study will be recorded on case report forms (CRFs), unless electronically transmitted to AstraZeneca or a designee (e.g., central laboratory). The investigator must maintain an accurate documentation (source data) to support the information entered in each CRF. The investigator must allow for monitoring, auditing, Institutional Review Board (IRB)/Independent Ethics Committee (IEC) review, and regulatory agency inspections related to the study, thereby providing direct access to source data files. Records and documents related to this study, including signed informed consent forms (ICFs), must be retained by the investigator for at least 25 years after study completion or as required by local regulations. Each subject was assigned a unique identifier to ensure privacy of the included participants. The data transmitted will not include the participant’s name or any personally identifiable information; only identifiers to distinguish the subjects will be used.

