### Sample size

2.6

The primary objective of this study was to demonstrate the non-inferiority of the FDC regimen of dapagliflozin/metformin XR to co-administered dual therapy of dapagliflozin and metformin for changes from baseline to week 24 in HbA1c within a non-inferiority margin of 0.30%, assuming a standard deviation of 1.2% (24). At a 1-sided significance level of 0.025, 253 patients per arm will be needed to provide 80% power (given a true difference of zero between the FDC regimen of dapagliflozin/metformin and XR and co-administered dual therapy of dapagliflozin and metformin). Assuming a dropout rate of 20%, 632 patients were randomized.

For the CGM sub-study, though exploratory in nature, the sample size was calculated based on exploratory hypothesis testing of the primary exploratory endpoint, which is the proportion of TITR (3.9-7.8 mmol/L) at week 12. Assuming a mean difference of 10%, standard deviation of 30%, and 2-sided significance level of 0.05, 143 patients per arm will provide 80% power for exploratory superiority testing. Assuming a dropout rate of 20%, approximately 358 patients were needed for the sub-study.

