The secondary endpoints will be analyzed in the PPS. An ANCOVA model will be used to analyze the absolute changes in FPG and PPG from baseline to week 24, reporting the point estimates of the average changes and two-sided 95% confidence intervals (CIs) within each treatment group as well as the differences in mean changes between groups. The difference in the proportion of patients achieving HbA1c levels below 7.0% at week 24 will be analyzed using logistic regression, adjusting for baseline HbA1c values. Participants with missing HbA1c measurements at week 24 will have the values imputed by dichotomizing the imputed HbA1c values at week 24. Odds ratios (ORs) and 95% confidence intervals will be reported. Descriptive statistics will be used for DQOL, DTSQ, and ARMS-D scores. An ANCOVA model will analyze the changes in the DQOL score from baseline to weeks 12 and 24. Point estimates of mean changes and 95% CIs within each group were calculated along with the differences in mean changes between the two groups. Differences in DTSQ and ARMS-D scores at week 24 between the two groups will be compared using the t-test or Wilcoxon rank-sum test, based on the normality and homogeneity of variances of the data.

The analyses for the primary and secondary endpoints will be repeated using FAS to examine the robustness of the results.

Exploratory endpoints will be analyzed based on the CGM analysis set. Point estimates and 95% CIs for all exploratory outcomes within each group were calculated along with estimates and 95% CIs for the differences between the two groups.

Safety analysis will be based on SS, summarizing the numbers and incidence rates of AEs, SAEs, and ADRs in each treatment group. At each scheduled time point, descriptive statistics will be used to summarize the values and changes from the baseline in vital signs, physical examinations, and clinical laboratory parameters within the different groups.

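### The data choose between a t-test and a Wilcoxon test for week-24 DTSQ and ARMS-D, so the quantity tested is not fixed and no between-group estimate is promised

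*Protocol article*

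**What the plan says.** Section 2.3 (Endpoints) of the protocol article defines the DTSQ and ARMS-D secondary endpoints as between-group differences at week 24. Section 2.7 (Statistical analysis) plans descriptive statistics for both scores and states that the group differences "will be compared using the t-test or Wilcoxon rank-sum test, based on the normality and homogeneity of variances of the data". It does not name the pre-tests or their cut-offs. Secondary endpoints are analysed in the per-protocol set, and the analyses are repeated in the full analysis set as a robustness check.

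The same section promises more for the other efficacy endpoints:

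- FPG, PPG and DQOL changes: ANCOVA with mean differences and 95% CIs.
- HbA1c below 7.0%: an odds ratio with 95% CI.
- Exploratory CGM outcomes: "Point estimates and 95% CIs for all exploratory outcomes within each group were calculated along with estimates and 95% CIs for the differences" between the groups.

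On timing, section 2.5 says "The patients completed the DQOL questionnaire at week 0 and the DTSQ, DQOL questionnaire, and ARMS-D at weeks 12 and 24". DTSQ and ARMS-D therefore have no baseline value.

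**The concern.** This is a rule that the article states, not a detail it leaves out. It raises three problems.

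1. **The target is not fixed.** One branch tests a mean difference, the other whether scores in one arm tend to rank higher. For an endpoint defined as a difference in scores, these are different questions with different matching estimates.
2. **The two analysis sets may take different branches.** A robustness check that changes both the patients and the test cannot show which of the two moved the result.
3. **Unequal variances are a stated ground for leaving the t-test, but Wilcoxon does not cure them.** If skewed scores have equal means and different spread, ranks differ systematically between arms, and the test rejects although the mean scores are the same.

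A difference in shape between arms is plausible here. The Discussion expects the open-label design to favour the FDC group on exactly these two scores. Scores pushed towards the end of a bounded scale change in spread as well as in location.

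At stake is the reading of the satisfaction and adherence results, both of which are named in the trial's title.

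**Working it through.** **Group size.** Section 2.6 plans the main study "within a non-inferiority margin of 0.30%, assuming a standard deviation of 1.2"%, one-sided alpha 0.025 and 80% power. The normal approximation gives 2 × (1.960 + 0.842)² × 1.2² / 0.30² = 251.2, so 252 per arm. The t-distribution gives 252.1, so 253, the stated figure. With 20% dropout, 506 / 0.8 = 632.5, against 632 stated. I use 253 per arm below.

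**Assumptions.** The documents give no mean, SD or shape for DTSQ or ARMS-D, so every distribution below is assumed. The pre-tests are assumed to be Shapiro-Wilk in each arm plus Levene, each at 0.05. If all pass, the t-test is used; otherwise Wilcoxon.

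**A hand check of the mechanism.** Take gamma-distributed scores with mean 5 in both arms and SDs of 4 and 5.

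- Arm A (SD 4): shape (5/4)² = 1.5625, scale 4²/5 = 3.2.
- Arm B (SD 5): shape 1, that is, exponential with mean 5.
- P(A > B) = 1 − (1 + 3.2/5)^(−1.5625) = 1 − 1.64^(−1.5625) = 1 − 0.4616 = 0.538. It would be 0.5 if neither arm tended to rank higher.
- Expected Wilcoxon z ≈ (0.538 − 0.5) × √(12 × 253 × 253 / 507) = 0.0384 × 38.92 = 1.49.
- Chance of rejecting ≈ Φ(1.49 − 1.96) = Φ(−0.47) ≈ 0.32.

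So about 32% of trials would report a difference although the means are equal.

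**Simulation, 253 per arm (3,000 to 6,000 trials per scenario and run).** Nominal level 5%.

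| Assumed scores | Rule rejects | Welch rejects |
|---|---|---|
| Same distribution, normal | 4.9% | 4.9% |
| Same distribution, bounded and skewed (DTSQ-like) | 5.0% | 5.1% |
| Same distribution, skewed counts (ARMS-D-like) | 5.2% | 5.2% |
| Same distribution, mild skew | 4.8% | 4.5% |
| Equal means, normal, SD 4 v 6 | 5.7% | 4.9% |
| Equal means, reversed gamma, SD 5 v 6 | 13.9% | 5.2% |
| Equal means, bounded 0–36, mean 30, SD 4 v 5 | 21% | 5% |
| Equal means, bounded 0–36, mean 30, SD 5 v 6 | 26% | 5% |
| Equal means, gamma mean 5, SD 4 v 5 | 31–33% | 4.5% |
| Equal means, gamma mean 5, SD 3 v 4 | 31–32% | 4.9–5.2% |
| Equal means, reversed gamma, SD 3 v 6 | 68.7% | 5.3% |

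In the gamma scenarios the rule chose Wilcoxon in every trial, because clearly skewed scores at this size always fail a normality test. The excess needs skew and unequal spread together; unequal spread alone (the normal row) does almost nothing.

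**Agreement between analysis sets.** With mildly skewed scores and assumed sizes of 300 per arm (full analysis set) and 253 per arm (per-protocol set), the two sets took different branches in 12 to 17% of trials. With strong skew both would go to Wilcoxon. Branch switching is thus a problem of mild skew, and excess rejection one of marked skew with unequal spread.

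**The case against.** The strongest defence is that, in a randomized trial with no treatment effect on the score, both arms have the same distribution, and there the rule keeps its level (4.8 to 5.2%). A difference in spread is itself a difference between the arms. Wilcoxon detecting it is an error only if the result is read as a difference in mean score. This stands. A reader might infer that the pre-test rule inflates false positives in general; the figures do not support that. The narrower point remains, because the article leaves open whether means or ranks are the target.

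The size also depends heavily on the assumed shape, from 5.7% to 68.7%, and the documents give nothing to narrow it. Descriptive summaries by arm are planned, and the article does not exclude a between-group CI; it only fails to state one where it does so for the other efficacy endpoints.

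Two further readings are tempting but do not hold:

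- **That the CGM endpoints are analysed without covariates.** Section 2.7 names no model for them and excludes no adjustment. The sub-study is exploratory, and an article may leave its model to the full protocol or analysis plan. Its unadjusted sample size is sound: with a 10-point difference and SD 30, the t-distribution gives 143 per arm, and 143 / 0.8 gives 179 per arm, 358 in total, as stated. Any gain from adjustment (power 82.0 to 94.1% for correlations of 0.2 to 0.6, against 80.5%) rests on correlations that the documents do not give.
- **That baseline data are wasted.** DTSQ and ARMS-D are first completed at week 12, and CGM is done only then: "At week 12 (± 5 days), CGM was performed for approximately five days". No baseline value of any of these measures exists to be discarded.

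**Conclusion.** The concern holds for DTSQ and ARMS-D only. The stated rule leaves open whether a mean difference or a rank shift is tested, can take different branches in the two analysis sets, and comes with no stated between-group estimate and interval.

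If the result is read as a difference in mean score, the rule can reject far too often: about 21 to 33% in the gamma and bounded scenarios with SDs differing by one point, against about 5% for Welch. The milder reversed-gamma case (SD 5 v 6) gives 13.9%. These rates are conditional on skewed scores with unequal spread, on assumed distributions and on assumed pre-tests. With identical distributions in the two arms the level is about 5%.

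The primary non-inferiority decision on HbA1c is untouched. This is a cheap improvement for two secondary endpoints, not a flaw that threatens the trial.

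**What to change.** Delete the data-dependent choice. Prespecify one primary analysis for week-24 DTSQ and ARMS-D, the same in both analysis sets: Welch's t-test, or a linear model with heteroscedasticity-robust standard errors, reporting the mean difference and its 95% CI. Keep the Wilcoxon test as a named sensitivity analysis, interpreted as a comparison of ranks.

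The cost is a change of wording, with no new data, visits or patients. The downside is a possible loss of power against a rank test if scores are strongly skewed and the treatment mainly shifts them; the sensitivity analysis would show this. The change should be fixed before the scores are compared by arm.

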## Discussion

3

T2DM is a significant global health issue, and poor glycemic control can lead to severe complications including chronic kidney disease, retinopathy, neuropathy, stroke, and myocardial infarction (25, 26). Therefore, controlling blood glucose levels and delaying the onset of complications is crucial for diabetes treatment. Recent clinical guidelines suggest that metformin and SGLT2 inhibitors can be used as initial dual therapy in patients with high HbA1c levels (2).

To date, studies comparing FDC to coadministration are rare. XIGDUO^®^ XR was launched in China in June 2023, and head-to-head clinical trials comparing the initial combination treatment with metformin and SGLT2 inhibitors with FDC therapy are still lacking. This study is a multicenter, non-inferiority, open-label randomized controlled trial designed to compare dapagliflozin/metformin XR FDC with co-administration of dapagliflozin and metformin XR in terms of glycemic control, patient satisfaction, quality of life, adherence to treatment, and safety in patients with newly diagnosed type 2 diabetes mellitus (T2DM). The primary endpoint focused on glycemic control efficacy, specifically the change in HbA1c from baseline after 24 weeks of treatment. Patient satisfaction, quality of life, and adherence to treatment were measured using the DTSQ, DQOL, and ARMS-D, respectively. The DTSQ has proven valuable for understanding and measuring patients’ treatment satisfaction in assessments of new treatments and strategies (27). DQOL, specifically developed to evaluate the quality of life of individuals with diabetes, is widely used and helps to understand how diabetes and its treatment impact the overall well-being and day-to-day experiences of patients (28, 29). The ARMS-D is a reliable and valid questionnaire designed to assess medication adherence in individuals with diabetes and helps healthcare providers identify adherence barriers and tailor interventions to improve compliance and health outcomes (30).

The multicenter design of this study enhances the generalizability and representativeness of the results. The change in HbA1c was used as the primary endpoint, as HbA1c reflects the patient’s blood glucose levels over the past 3–4 months and is considered the gold standard for blood glucose control. Therefore, the study endpoint reflects the effect of glycemic control. Additionally, CGM was employed as an exploratory study to assess glucose variability in more detail, offering deeper insights into future treatment strategies.

This study had several limitations. First, the open-label design may introduce a potential positive bias toward the FDC group, particularly concerning the DTSQ and ARMS-D scores, given the known convenience of a single tablet regimen. Second, the 24-week duration of the trial limited our ability to assess long-term outcomes, including the trajectory of β-cell function, sustainability of glycemic control, and more comprehensive safety profile. Third, the recruitment of participants exclusively from Chinese centers may limit the generalizability of our findings to other ethnic groups and healthcare settings. While this focus provides highly relevant data for the Chinese population, future multinational studies are warranted to confirm the global applicability of the results.

In conclusion, as the first study to directly compare the dapagliflozin/metformin XR FDC with the separate administration of dapagliflozin and metformin hydrochloride XR, this scientifically designed trial has the potential to provide crucial evidence supporting the use of FDCs. Additionally, it may offer valuable insights for physicians in selecting treatment regimens for diabetes and in improving patient adherence.
